**SYNOPSIS FOR « ClinicalTrials.gov**. **» REGISTRATION**

x **Study Type** **Interventional:** *studies in human beings in which individuals are assigned by an investigator based on a protocol to receive specific interventions. Subjects may receive diagnostic, therapeutic or other types of interventions. The assignment of the intervention may or may not be random. The individuals are then followed and biomedical and/or health outcomes are assessed.*

| **Official Title** | Short-term GnRH- antagonist treatment to lower LH pulsatility in women with PCOS aiming to improve hormonal functions |
| --- | --- |
| **Brief Title** | Sub-therapeutic GnRH- antagonist treatment to rectify LH pulsatility in lean women with PCOS. |
| **Acronym** | SOPKGANI |
| **Collaborators** | ERC GRASP (PoC) |
| **Brief summary** | We will conduct a clinical study using a sub-therapeutic dose of a GnRH antagonist to reduce overactive LH pulsatility in women with PCOS. With the intervention and lowered LH action we anticipate to decrease androgen levels in women with PCOS. We aim to show for the first time that low-dose GnRH-antagonists can lower LH pulsatility by 20–30% and decrease androgen levels without blunting the hypothalamic-pituitary-gonadal axis and thereby the reproductive functions. |
| **Conditions** | Polycystic Ovary Syndrome |
| **Keys Words** | PCOS ; GnRH antagonist ; LH ; androgen ; testosterone |
| **Primary purpose** | Treatment  Prevention  Diagnostic  Supportive care  Screening  Health services Research  Basic science  Other |
| **Intervention model** | Single group  Parallel  Crossover  Factorial |
| **Study classification** | Safety  Safety/Efficacy  Efficacy  Bio-equivalence  Bio-availability  Pharmacokinetics  Pharmacokinetics/dynamics  Pharmacodynamics |
| **Interventions (repeating as many times as arms)** | |
| **Name of arm 1** | Pilot phase-0, parallel, clinical study.  Test the efficacy of Ganirelix administered subcutaneously at single-dose regimen of 0.0625 mg in 10 women with PCOS, in rectifying LH pulse frequency and LH amplitude. |
| **Intervention (at least one intervention)** | Drug (including placebo)  Radiation  Other  Device (including sham) Behavioral  Biological / vaccine  Genetic  Procedure / surgery  Dietary supplement |
| **Intervention name** | Ganirelix (Orgalutran) |
| **Intervention description** | An intra-venous cannula will be inserted and blood will be sampled at 10-min intervals for a 4-h baseline period commencing at 0800 h. Ganirelix will be then administered subcutaneously at single-dose regimen at 0.0625 mg (n = 10 women with PCOS). After Ganirelix administration sampling will continue at 10-min intervals for 4 h. |
| **Name of arm 2** | Pilot phase-0, parallel, clinical study.  Test the efficacy of Ganirelix administered subcutaneously at single-dose regimen of 0.025 mg in 10 women with PCOS, in rectifying LH pulse frequency and LH amplitude. |
| **Intervention (at least one intervention)** | Drug (including placebo)  Radiation  Other  Device (including sham) Behavioral  Biological / vaccine  Genetic  Procedure / surgery  Dietary supplement |
| **Intervention name** | Ganirelix (Orgalutran) |
| **Intervention description** | An intra-venous cannula will be inserted and blood will be sampled at 10-min intervals for a 4-h baseline period commencing at 0800 h. Ganirelix will be then administered subcutaneously at single-dose regimen at 0.025 mg (n = 10 women with PCOS). After Ganirelix administration sampling will continue at 10-min intervals for 4 h. |
|  | **Primary Outcome measure** |
| **Title** | Serum LH level every 10 minutes for 8 hours |
| **Time point at which primary outcome measure is assessed** | The degree of gonadotropin suppression will be determined by calculating the percent inhibition from the pre-antagonist period [(mean PRE - nadir)/mean PRE] x 100, where nadir hormone levels will be calculated using a moving average. |
|  | **Secondary outcome measures, repeating as many times as 2nd outcomes** *Noter les 5 principaux critères d’évaluation* |
| **Title** | Measurement of serum testosterone and androstenedione, FSH, estradiol and AMH levels |
| **Time point(s) at which Secondary outcome measure is assessed** | Serum testosterone and androstenedione, FSH, AMH and estradiol levels at the beginning and at the end of the 8 hours |
| **Inclusion criteria** | -women aged 18 to 35  -women with PCOS with AMH> 28 pmol / L, LH> 8 IU / mL and testosteronemia > 0.39 ng/mL  - no hormonal treatment or contraception for 2 months  - women covered by the Social Security system  Non obese women |
| **Exclusion criteria** | -hormonal treatment or hormonal contraception  - Metformin treatment  -pregnant woman  -inability to understand the newsletter |

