### ****7.2 Study Procedures****

This is a **phase 1 pilot study** with **two parallel groups**, evaluating the efficacy of two different doses of Ganirelix in **20 women with PCOS**, defined by **oligo-/anovulation**, **hyperandrogenism**, and **elevated circulating LH levels**.

An **intravenous cannula** will be inserted, and **blood samples will be collected every 10 minutes** for a **4-hour baseline period** starting at 8:00 a.m.
Subsequently, Ganirelix will be administered as a **single subcutaneous injection** at one of two doses:

- **0.025 mg** (n = 10 PCOS patients)
- **0.0625 mg** (n = 10 PCOS patients)

These doses correspond to approximately **one-tenth and one-quarter** of the standard clinical dose used in **IVF protocols** to achieve full LH suppression.

Following Ganirelix administration, blood sampling will continue every 10 minutes for an additional **4-hour period**.

The **primary endpoints** include mean LH levels, as well as LH pulse **frequency and amplitude**, evaluated before and during treatment with Ganirelix.
In healthy women, LH surges occur approximately every 90 minutes during the early follicular phase, whereas **lean women with PCOS** may exhibit **one or more LH pulses per hour**.

The expected outcome is to determine the Ganirelix dose that reduces the **abnormally elevated frequency** of LH pulses by approximately **20–30%**, bringing them closer to normal physiological values.

**Secondary outcomes** include reproductive hormone markers — **serum testosterone, androstenedione, LH, FSH, estradiol, and AMH levels** — measured before treatment and **4 hours post-injection**.

The **pretreatment period** (baseline LH secretion and pulsatility) will be compared to the **4-hour post-antagonist period.**An **LH pulse** will be defined as a **≥20% incremental change** in LH concentration between the nadir and the subsequent peak, as previously described in similar clinical studies (Ref. 25).

The degree of gonadotropin suppression will be calculated as a **percentage of inhibition** relative to the pre-antagonist period:

$$\text{Inhibition (\%)}=\frac{(\text{PRE mean}-\text{nadir})}{\text{PRE mean}}\times100$$

as described previously (Ref. 26).
Hormone nadir levels will be computed using a **moving average**.
For LH, a **6-point moving average** (equivalent to 1 hour of sampling) will be used, as the nadir is expected to occur within the 10-minute sampling intervals.

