# BIOLOGICAL ANALYSES

**Routine Clinical Tests and Study-Specific Biological Analyses**

All laboratory analyses will be conducted under the supervision of **[name] [name]**, Department of **Hormonology, Nutrition, and Oncology**, at the**Institute of Biochemistry and Molecular Biology**, within the **Biology, Pathology, and Genetics Division** of **Lille University Hospital (CHU de Lille).**

| **Parameters to be Analyzed** | **Baseline (T0)** | **Intermediate Time Points (every 10 min for 8 h)** | **Final Time Point (T0 + 8 h)** | **Use (Clinical/Research)** | **Location & Responsible Unit** |
| --- | --- | --- | --- | --- | --- |
| LH | — | 1 dry tube (1.5 mL) at each time point | — | Research | CBP Biochemistry Laboratory |
| LH, FSH, Estradiol, Total Testosterone | 1 dry tube (5 mL) | — | 1 dry tube (5 mL) | Research | CBP Biochemistry Laboratory |
| AMH | 1 dry tube (5 mL) | — | 1 dry tube (5 mL) | Research | CBP Biochemistry Laboratory |
| Androstenedione | 1 dry tube (5 mL) | — | 1 dry tube (5 mL) | Research | CBP Biochemistry Laboratory |
| **Total** | **3 dry tubes (5 mL)** | **49 dry tubes (1.5 mL)** | **3 dry tubes (5 mL)** | **Research** | **CBP Biochemistry Laboratory** |

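### The percent-inhibition index sets a pre-injection mean against a post-injection minimum, so it is above zero even when the drug does nothing

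*Protocol*

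**What the plan says.** Two places in the protocol define the index.

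- **Synopsis for ClinicalTrials.gov registration, primary outcome measure.** The outcome's title is serial serum LH. The row for the time point gives percent inhibition from the pre-antagonist period through the expression "mean PRE - nadir)/mean PRE] x 100, where nadir hormone levels will be calculated using a moving average".
- **Section 7.2, Study Procedures.** "The degree of gonadotropin suppression will be calculated as a" percentage by the same formula, with reference to an earlier published study. For LH the nadir comes from a "6-point moving average", that is one hour of sampling, "as the nadir is expected to occur within the 10-minute sampling intervals".

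Sampling is every 10 minutes throughout: "After Ganirelix administration sampling will continue at 10-min intervals for 4 h". The table of biological analyses counts "49 dry tubes (1.5 mL" each) per woman.

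No nadir is defined for the pre-injection period. There is no untreated or placebo group; section 5.2 relies on each woman being her own control. Elsewhere (section 4.1 and the primary endpoint paragraph of the statistical section) the primary endpoint is LH pulse frequency. Section 4.2 separately plans mean, basal and total LH before and after injection.

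**The concern.** Self-control removes bias when the same statistic is computed before and after treatment. Here it is not: an average stands on one side and a minimum on the other. LH in these women is pulsatile by the protocol's own account ("one or more LH pulses per hour"), so some hours are always lower than others. Picking the lowest hour after injection and comparing it with the whole 4-hour baseline gives apparent inhibition in a woman who received nothing.

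At stake is what is reported as the degree of suppression at each dose. The statistical section promises estimates with 95% confidence intervals, and a reader will take zero as the no-effect value. For this index zero is not that value, and nothing in the design estimates what it is.

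**Working it through.** **Inputs from the protocol.** 49 LH values at 10-minute spacing, taken as 25 PRE (including the sample at injection) and 24 POST; a 6-point window; pulses at least hourly; a pulse is a "≥20% incremental change" from nadir to peak (section 7.2). The protocol states no expected value of the index, so there is no figure to reproduce. The nadir is taken to be post-injection, which the formula implies but does not say.

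**Step 1: the sign, without any assumption about LH.** 24 POST values give 24 − 6 + 1 = 19 overlapping windows. Four of them are disjoint and cover the whole period, and their average is the POST mean. Hence

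lowest of 19 windows ≤ lowest of 4 disjoint hours ≤ POST mean.

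So

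index − 100 × (PRE mean − POST mean)/PRE mean = 100 × (POST mean − nadir)/PRE mean ≥ 0,

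with equality only if every one-hour window has the same mean. The index can never be smaller than the mean-to-mean change in the same woman.

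**Step 2: the size with no drug effect.** This needs assumptions that are not in the protocol: LH half-life 60 or 90 minutes, assay CV 5%, pulse-interval CV 0 to 0.35, pulse-amplitude CV 0 to 0.5, mean increment 20% to 100%. Index = 100 × (1 − lowest 6-point average of 24 POST values / mean of 25 PRE values).

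| No-drug model | Mean index |
|---|---|
| Independent values, CV 5, 10, 15, 20, 25, 30% | 2.9, 5.7, 8.4, 11.1, 13.8, 16.5% |
| Autocorrelated values, CV 10 to 30% | 6.8 to 22% |
| Pulses every 45 or 60 min, increment 20 to 80% | 2.7 to 20% (median 8.0%, quartiles 5.9 and 12.2%) |
| Same intervals, increment 100%, amplitude CV 50% | 13 to 25% |
| Perfectly regular, equal 60-min pulses | about 3% |

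The last row is low because a one-hour window then spans exactly one pulse. One setting as an example: 60-minute intervals (CV 0.2), increment 50% (CV 0.4), half-life 60 minutes gives a mean index of 12.1%, and 27% of untreated women show 20% or more. Across the settings at 45 to 60 minutes with increments of 20 to 80%, that share runs from 0% to about 55%. Counting the injection-time sample in both periods adds at most about 0.7 points.

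**Step 3: like-for-like contrasts on the same kind of series.** POST mean against PRE mean, as a geometric mean ratio, gives about −1% to +1%. POST nadir against PRE nadir over equal 24-point windows gives −5% to 0% when percentages are averaged, and about 0% as a log ratio; the negative values come from averaging skewed ratios.

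**Step 4: arms of 10 women.** With 45- or 60-minute intervals, increments of 20 to 80%, half-life 80 minutes and assay CV 5%, the 95% interval for the mean index lies wholly above zero in 64% to 100% of arms without drug effect. For PRE mean against POST mean the interval excludes zero in 2% to 8%, near the nominal 5%.

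**Step 5: the dose contrast.** Let b be the no-drug offset and s the true proportional suppression, with the relative pulse pattern unchanged. Then index = 1 − (1 − s)(1 − b) = s + b(1 − s). Between doses the difference is (s₁ − s₂)(1 − b): zero if the doses are equal, and otherwise shrunk by the factor 1 − b, that is 0.97 to 0.75 for b of 0.03 to 0.25.

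**The case against.** The strongest reply concerns the role of the index. The body of the protocol makes pulse frequency primary, and the statistical section never uses the index. No test, success rule or dose choice is tied to it, the study is described as exploratory, and mean, basal and total LH before and after injection are already planned. All of this stands. A reader might infer that the trial's primary analysis is biased, or that the public registry entry is. The documents support neither: pulse frequency does not depend on the index, and only a registration synopsis is at hand, not the registry record.

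A second reply is that the index follows a cited precedent and aims at maximal rather than average suppression. That is a legitimate aim. The product information in Annex 4 puts peak concentration at 1 to 2 hours, so a 4-hour POST mean includes the absorption phase and answers a different question. This argues for keeping a nadir, but for taking it on both sides. Precedent does not change step 1.

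Third, the size is uncertain. A reader might settle on a narrow band such as 9% to 16%; only about a third of the pulsatile settings with increments of 20 to 80% fall there. A reader might also set the offset against the 20–30% target and call it half of the effect sought. The protocol states that target chiefly for pulse frequency, loosely for mean and basal LH in the synopsis, and never for this index, so the two cannot be put on one scale.

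**Conclusion.** The concern holds for the reading of suppression within an arm. That the index lies at or above the mean-to-mean change follows from the formula alone; that its no-drug value is above zero needs only that LH varies from hour to hour around a stable level. The size, about 3% to 25%, rests on assumed pulse size, pulse regularity and assay error and should be quoted only as that range. With no untreated arm the trial cannot subtract the offset, and with 10 women per dose an inactive dose would usually give a confidence interval above zero. The comparison of doses is largely spared, and the pulse-frequency endpoint is untouched.

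**What to change.** In the primary outcome entry of the registration synopsis and in section 7.2, replace the index with a like-for-like contrast within each woman, analysed as a log ratio and reported as a percentage with its 95% interval. Two forms would serve:

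- POST mean against PRE mean, which secondary endpoint 1 already plans; or
- to keep a measure of maximal suppression, POST nadir against PRE nadir, each from the same 6-point moving average over windows of equal length (24 values each, with the injection-time sample assigned to one period only).

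If the published index is kept for comparison with earlier work, state that its nadir is post-injection, label it descriptive, and print beside it the same index computed within the pre-injection window as its no-drug reference. Under the assumptions of step 4 that reference came within about 2 points of the no-drug value.

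The cost is wording in two places and a few lines of calculation on LH values already collected. The drawback is that the reported suppression will be smaller and less directly comparable with the cited study.

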# SCIENTIFIC RATIONALE

### ****Polycystic Ovary Syndrome (PCOS)****

Polycystic Ovary Syndrome (PCOS) is the most common reproductive and metabolic disorder, affecting up to 18% of women worldwide, and is responsible for about 70% of cases of anovulatory infertility¹^,^². This endocrine disorder is present throughout a woman’s life, has a noticeable impact on quality of life, and represents a significant clinical, psychological, and economic “burden.” It is frequently associated with considerable medium- and long-term morbidities: pregnancy-related complications, placental dysfunction, increased obstetric morbidity (gestational diabetes, preeclampsia, preterm birth), obesity, type 2 diabetes, hepatic steatosis, and an increased risk of neuropsychiatric disorders ³.

In the United States alone, health care expenditures related to PCOS among women of reproductive age were estimated to exceed $5 billion per year in 2019 ⁴. Comparable data are not available for Europe, but it is likely that the health care costs associated with PCOS exceed €1 billion annually.

The diagnostic criteria for PCOS have been revised several times — by the Rotterdam consensus, the Androgen Excess and PCOS (AE-PCOS) Society, and the National Institutes of Health (NIH). There is no universally accepted version, although an international evidence-based guideline for the assessment and management of PCOS⁵ endorses the use of the Rotterdam diagnostic criteria. According to these criteria, a woman must meet two of the following three criteria for a diagnosis of PCOS: oligomenorrhea or amenorrhea; biochemical or clinical evidence of hyperandrogenism (specifically hirsutism and acne); and typical ultrasound features of polycystic ovaries. The Rotterdam criteria yield four PCOS phenotypes:

- **Type A (classic PCOS):** hyperandrogenism (HA) + irregular/absent menstrual cycles (ovulatory dysfunction, OD) + polycystic ovarian morphology (PCOM);
- **Type B:** HA + OD;
- **Type C:** HA + PCOM;
- **Type D:** OD + PCOM.

Elevated androgens represent a major feature of PCOS, as the majority (nearly 80%) of women with PCOS have hyperandrogenism (Rotterdam definition) ⁶. Moreover, most women (75%) diagnosed with PCOS show accelerated LH pulsatility, independent of obesity status ⁷^,^⁸, suggesting a rapid frequency of GnRH pulsatility ⁹^,^¹⁰.

Although the defining features of PCOS (i.e., androgen excess, oligo-/anovulation, and polycystic ovarian morphology) are most directly related to ovarian function, the central reproductive neuroendocrine system — the gonadotropin-releasing hormone (GnRH) — ultimately determines ovarian function through its regulation of gonadotropin release. Altered GnRH secretion plays a significant role in the pathophysiology of PCOS ¹¹.

Previous work by the [name] group has shown that anti-Müllerian hormone (AMH) induces LH secretion by stimulating activation and secretion of neuropeptides in GnRH neurons ¹², which express AMH receptors in both rodents and humans ¹²-¹⁴. AMH is secreted by granulosa cells of ovarian follicles ¹⁵ and regulates early follicular development by influencing the transition from resting primordial follicles to growing follicles ¹⁶.

Earlier studies have shown that plasma AMH levels in patients with PCOS are 2–3 times higher than those in women with normal ovaries ¹⁷^,^¹⁸, and that the severity of the PCOS phenotype correlates with AMH production — higher in anovulatory PCOS patients than in ovulatory ones ¹⁹^,^²⁰. Furthermore, the [name] and Piltonen groups have shown in two collaborative studies that elevated AMH levels persist throughout pregnancy in women with PCOS compared with gestational-age– and weight-matched non-PCOS controls ¹⁴^,^²¹.

Animal models have contributed to a better understanding of the etiopathogenesis of PCOS and its underlying pathophysiological mechanisms, confirming the central role of hyperandrogenism in the development of this condition. Indeed, PCOS models generated by inducing hyperandrogenism consistently produce animals exhibiting a wide range of reproductive, endocrine, and metabolic features of PCOS ¹. Prenatal exposure to testosterone or early postnatal exposure to dihydrotestosterone (DHT) has been reported to generate a PCOS-like phenotype in rodents (the PNA model), as well as in sheep and non-human primates ¹.

Recent studies from the [name] group have implicated AMH signaling in the brain as a potential player in the development and pathophysiology of PCOS ¹⁴^,^²². Pregnant mice injected with AMH showed increased testosterone production, reduced placental conversion of testosterone to estradiol, and offspring (the PAMH model) predisposed to PCOS-like features after puberty ¹⁴. These studies suggest that prenatal AMH treatment promotes remodeling of placental steroidogenesis, leading to inhibition of aromatase expression and thereby increasing in utero testosterone bioavailability. These findings are consistent with clinical investigations showing reduced placental aromatase activity in women with PCOS ²³.

AMH-induced androgenization may also rely on central AMH actions that enhance GnRH release, since PAMH mothers also display elevated LH and testosterone levels at term ¹⁴, similar to findings in humans ²¹.

We have observed that PCOS-like females exhibit persistent hyperactivity of GnRH neurons and that treatment with a GnRH antagonist in adult female offspring restores their neuroendocrine phenotype to normal. These findings highlight the critical role of excessive prenatal AMH exposure and hyperstimulation of GnRH receptors in the neuroendocrine dysfunctions of PCOS, while offering a new potential therapeutic avenue for treating this condition in adulthood.

It is important to note that in women with PCOS, long-acting GnRH agonists — which suppress gonadotropin secretion — significantly reduce circulating androgen concentrations. Likewise, suppression of gonadotropins partly explains the effectiveness of combined oral contraceptives in treating PCOS-related hyperandrogenism ²⁴.

Based on the above preclinical and clinical evidence, and the established safety of GnRH antagonists (FDA-approved), we are confident that a clinical trial using a low-dose GnRH antagonist to reduce hyperactive LH pulsatility in women with PCOS should yield significant beneficial effects associated with normalization of abnormal androgen and LH levels.

# STUDY OBJECTIVES

### ****3.1 Primary Objective****

To assess the effect of Ganirelix on the reduction of luteinizing hormone (LH) pulse frequency, comparing two different dose levels.

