# EVALUATION CRITERIA

### ****4.1 Endpoint for the Primary Objective****

The expected decrease in LH pulse frequency before and after Ganirelix* administration is estimated to be between 20% and 30%.
To be considered an LH pulse or peak, the value had to show an increase of more than 20% compared with one of the two preceding points, followed by a decrease of more than 10% in one of the two subsequent points.

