# METHODOLOGY

### ****5.1 Study Design****

This is a **single-center, phase I pilot study** with **two parallel groups**.

The study will be proposed during endocrinological gynecology consultations to all patients meeting the inclusion criteria. After obtaining written informed consent, participants will be assigned to one of the two dose groups.

During the 4 hours preceding Ganirelix injection*, baseline LH secretion and pulsatility, as well as baseline levels of androgens, FSH, estradiol, and AMH, will be measured.

Subsequently, patients will receive a **low-dose injection of Ganirelix***. LH secretion and pulsatility will be monitored for **4 hours following the injection**, along with measurements of androgens, FSH, estradiol, and AMH at **H8**.

The expected outcome is to identify the Ganirelix* dose that reduces the abnormal frequency of LH pulses in women with PCOS to values comparable to normal conditions (approximately a 30% reduction).

As **secondary outcomes**, reproductive markers (serum levels of testosterone, androstenedione, LH, FSH, estradiol, and AMH) as well as glucose, insulin, and liver function parameters will be assessed before and after the 4-hour GnRH antagonist treatment period.

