### ****5.2 Measures Taken to Minimize Bias****

Each participant will serve as her own control in this study, thereby minimizing potential bias.

The phenotypic diversity among women with PCOS — particularly regarding lean versus obese status — has a significant impact on mean plasma LH levels. To reduce variability, this pilot study will focus exclusively on **lean women with a highly uniform PCOS phenotype**, defined as follows:

- Age between **18 and 35 years**,
- **BMI below 30 kg/m²**,
- **Hyperandrogenism** (total testosterone > 0.39 ng/mL),
- **Elevated plasma LH** (> 8 IU/mL),
- **Elevated plasma AMH** (> 28 pmol/L).

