# STATISTICAL ANALYSES

**General Principles**
All statistical analyses will be performed independently by the Department of Biostatistics, University of Lille, under the supervision of [name]. Analyses will be conducted using 10.0.2 GraphPad Prism software (GraphPad; San Diego, CA, USA).

All analyses will be performed on the per-protocol population, unless otherwise specified. The level of statistical significance will be set at α = 0.05 (two-sided). No adjustment for multiple testing will be applied, and all secondary analyses will be considered exploratory. Results will be presented as effect size estimates with corresponding 95% confidence intervals (95% CI).

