**Description of Data**
Baseline demographic and clinical characteristics will be described by treatment group.
Quantitative variables will be summarized as mean (standard deviation or standard error). The normality of data distributions will be evaluated using the Shapiro–Wilk test.

For normally-distributed data, data will be compared using unpaired two-sided Student’s *t*-test. For non-normally distributed values, Mann-Whitney U test will be used.

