**Primary Endpoint Analysis**
The primary endpoint is the reduction in LH pulse frequency during the 4-hour period following Ganirelix administration.
Analysis will include:
- Determination of LH pulse frequency using the method described above (1.1.2).

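### The primary contrast for LH pulse frequency is inconsistent: section 3.1 compares doses, sections 4.1, 5.2 and 7.2 compare before with after, and only unpaired tests are named

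*Protocol*

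**What the plan says.** Keep the endpoint at LH pulse frequency throughout. The protocol then describes three different comparisons.

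- **Dose against dose.** Section 3.1: "To assess the effect of Ganirelix on the reduction of luteinizing hormone (LH) pulse frequency, comparing two different dose levels". The synopsis states the same objective without the comparing clause; it speaks only of an effect studied with two doses.
- **Before against after.** Section 4.1: "The expected decrease in LH pulse frequency before and after Ganirelix* administration is estimated to be between 20% and 30" per cent. Section 5.2: "Each participant will serve as her own control in this study, thereby minimizing potential bias". Section 7.2 says of the pretreatment period: "baseline LH secretion and pulsatility) will be compared to the" four hours after the antagonist.
- **Finding one dose.** Section 5.1: "The expected outcome is to identify the Ganirelix* dose that reduces the abnormal frequency of LH pulses in women with PCOS" to near-normal values, about 30%. Section 7.2 repeats this with 20–30%.

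The Statistical Analyses section does not settle the matter. Under Description of Data it says "For normally-distributed data, data will be compared using unpaired two-sided Student’s" t-test, with Mann-Whitney U for non-normal values. Under Primary Endpoint Analysis it calls the endpoint a reduction and lists a single item: "Determination of LH pulse frequency using the method described above (1.1.2"). General Principles sets two-sided 0.05 and adds: "No adjustment for multiple testing will be applied, and all secondary analyses will be considered exploratory". The justification for having no power calculation calls the whole study exploratory, favours estimation over hypothesis testing, and says the results will support a later confirmatory trial.

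Section 5.2.1 assigns the first 10 women to one dose and the next 10 to the other, without randomisation.

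**The concern.** The design and endpoint sections point to a paired comparison within each woman, while the objective and the named tests point to a comparison of independent groups. An analyst who follows section 3.1 and Description of Data would run an unpaired test between doses. One who follows 4.1, 5.2 and 7.2 would need a paired method that the protocol does not name. Nothing says whether the before/after change is estimated in each dose group or over all 20 women, or what is concluded if both doses, or neither, reach the target.

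The dose-identification wording adds a further risk. It invites setting two within-dose results side by side and naming the dose that is significant, or in the band, when the other is not. That pattern is not evidence that the doses differ. A dose named in this way could be carried into the confirmatory trial.

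**Working it through.** The protocol gives no SD, power or sample-size formula, so it has no figure of its own to reproduce.

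**Inputs**
- n = 10 per dose (section 5.3); two-sided 0.05 (General Principles); target band 20–30% (section 4.1).
- Baseline 4 pulses per 4 hours. This is assumed, at the lower end of the one or more pulses per hour given for lean women with PCOS in section 7.2.
- SD of the within-woman change 0.75 to 1.5 pulses. This is assumed, as the protocol gives none.
- Changes treated as normal, although real counts are small integers.
- Both doses truly lower frequency by 25%, that is by 1 pulse.

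**Exactly one mean in the band.** The band is 0.8 to 1.2 pulses, so a group mean is in it with probability q = 2Φ(0.2 / (SD/√10)) − 1. Exactly one of two equal doses is in the band with probability 2q(1 − q). At SD 1.0: 0.2/0.316 = 0.632, q = 0.473, and 2 × 0.473 × 0.527 = 0.50.

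**Exactly one dose significant.** The power p of a paired t-test on 9 df comes from the noncentral t with noncentrality √10/SD. Exactly one is significant with probability 2p(1 − p). At SD 0.75: p = 0.962, and 2 × 0.962 × 0.038 = 0.073.

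**Precision of the dose difference.** The 95% half-width is 2.101 × SD × √(2/10), divided by 4 to express it as a share of baseline. At SD 1.0: 2.101 × 1.0 × 0.447 / 4 = 23.5%.

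| SD of change | q | Exactly one mean in band | p | Exactly one significant | Half-width, dose difference (% of baseline) |
|---|---|---|---|---|---|
| 0.75 | 0.601 | 48% | 0.96 | 7% | 18 |
| 1.0 | 0.473 | 50% | 0.80 | 32% | 23 |
| 1.25 | 0.387 | 47% | 0.62 | 47% | 29 |
| 1.5 | 0.327 | 44% | 0.47 | 50% | 35 |

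Simulation with 20,000 data sets per scenario shows how often the readings diverge. With both doses at −25%, at least one before/after test is significant while the dose comparison is not in 95%, 91%, 81% and 67% of trials at the four SDs.

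**If the doses do differ.** Suppose the true reductions are 20% and 30%, a difference of 0.4 pulse. Power for the dose comparison at 10 per arm is then 20%, 14%, 10% and 9% at the four SDs, and 80% power would need 56, 99, 154 and 221 per arm.

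**Assignment.** Any dose contrast sets the first 10 women enrolled against the next 10, so it cannot be separated from changes over the recruitment period. The before/after contrast within one woman does not depend on that assignment.

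**The case against.** The strongest reply is that before/after plainly dominates. It appears in 4.1, 5.2 and 7.2, and the word reduction in the primary analysis paragraph implies a pre-injection reference. The dose-versus-dose objective rests on one clause in 3.1 that the synopsis lacks, and dose identification is called an expected outcome, not a decision rule. This stands in part: the protocol does describe a leading contrast. It does not name it as primary, say per dose or pooled, or supply a test that fits it. The unpaired tests could be meant only for describing the groups, but then no test is named for the primary endpoint at all.

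A second reply is that the study is exploratory and built for estimation. That also stands, and it lowers the stakes. An estimation study must still say what it estimates, and this one also sets a significance level and names tests.

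Three stronger readings are tempting, and the documents do not support them.

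- *The readings give opposite conclusions.* A fall at both doses and no demonstrated dose difference answer different questions and are compatible. Non-significance between doses does not show that dose has no effect.
- *The type I error is inflated and needs an alpha split.* Two independent within-dose tests would give 1 − 0.95² = 9.75%, but the protocol names no paired or pooled test, so that family is the reader's construction. In an exploratory pilot the adjustment is a trade-off: testing each dose at 0.025 would raise the chance that exactly one is significant from 32% to 43% at SD 1.0.
- *The 20–30% band is a pass/fail rule.* Section 4.1 states an expectation. The 44–50% figure shows what happens if the band is used to pick a dose, as the identification wording invites.

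**Conclusion.** The inconsistency is real and lies within the protocol's own text; a separate analysis plan could resolve it only by overriding some of that text. Followed as written, the study could answer its primary question with a non-randomised, imprecise dose contrast, or name one of two equally effective doses.

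If both doses lower frequency by 25%, choosing by the band separates them in about 44–50% of trials, a figure that moves little over the assumed SDs. Choosing by significance separates them in about 7–50%, and this depends heavily on the SD: at 0.75 it is a minor problem. Both ranges rest on the assumed baseline of 4, the assumed SDs and normal changes. The finding itself does not; it rests on the mismatch between sections. It should be corrected, with modest weight given the exploratory purpose.

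**What to change.** - In 3.1, 4.1 and Primary Endpoint Analysis, state that the primary contrast is the within-woman post-minus-pre change in LH pulse frequency, estimated in each dose group with a 95% CI and analysed by a paired method (paired t or Wilcoxon signed-rank).
- In Description of Data, limit the unpaired t and Mann-Whitney tests to between-dose comparisons of change.
- Make the between-dose difference in change, with its 95% CI, a secondary, descriptive estimate, and note beside it that dose was assigned in sequence without randomisation.
- In 5.1 and 7.2, replace the aim of identifying the dose with *estimate the change at each dose*.
- State that no claim that one dose works better will rest on one dose being significant, or in the 20–30% band, and the other not.

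No alpha split is needed. The cost is wording: no added women, samples or assays. The study gives up a dose-identification claim, which 10 women per dose cannot support.
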